## **8.Theory evidence**

Based on clinical practice, the team searches domestic and international databases to summarize the best evidence based on evidence-based, and develops pain management strategies based on the SMT theoretical framework. The theory focuses on managing patients' symptoms and consists of symptom experience, symptom management strategies and symptom outcomes. In the ICU, in response to pain in patients with SAP, SMT provides a structured approach to identifying pain symptoms by assessing pain levels on a regular basis using the VAS-P or patient self-report, recording scores, and thus understanding the patient's symptom experience. Based on these assessments, a 6W2H pain symptom management strategy was developed to individualize symptom management. The strategy consisted of two regimens of continuous epidural pumping of combination medications and on-demand intermittent epidural injections of 5 ml of combination medications on top of this. The key elements of why (purpose), who ( in charge), who (subject), where ( location), when ( timing), what ( measures), how ( methods), and how much ( frequency) were specified. Symptom outcome refers to the assessment of the effectiveness of the symptom management strategy after its implementation. In this study, the effectiveness of pain management was assessed primarily through indicators such as pain scores, dosage of combination medications, incidence of adverse events, length of stay in the ICU, mortality, and patient pain satisfaction. By recording and analyzing these indicators, the effectiveness and safety of different analgesic regimens were assessed to provide a scientific basis for optimizing pain management regimens. A comprehensive baseline assessment of other factors affecting pain, including person, environment and health/illness will be conducted to ensure consistent patient inclusion criteria. The SMT-based pain management framework for SAP patients is shown in [Figure 1](#).

[figure not shown]

Figure 1: Framework of Pain Management in SAP Patients Based on Symptom Management Theory (SMT)

## 9. Research team and implementation process

The study team consisted of 14 multidisciplinary members, including two project managers, two anesthesiologists, three ward clinical physicians, five pain management nurses, and two data collection researchers.

The project manager was responsible for the training and supervision of the pain management strategy to ensure that the nurses were competent in implementing the strategy and meeting the requirements of the study protocol. The anesthesiologist was responsible for epidural placement, providing technical support to ensure patient comfort and safety, and assisting in the development of the analgesic protocol. The ward clinical physicians were responsible for the daily medical management of patients, handling emergencies, ensuring patient safety, and participating in the development and adjustment of the pain management program. Pain management nurses, based on SMT, lead the implementation of pain assessment and management strategies for SAP patients in the ICU, record pain scores, perform TEA drug administration, handle patients' pain feedback, closely observe pain responses, communicate with physicians in a timely manner, ensure effective implementation of the pain management program, and record adverse reactions. The data collection researcher is responsible for collecting study data, including pain scores and adverse events, ensuring data accuracy and completeness, performing data quality control and analysis, using professional statistical software to analyze the data, and providing data analysis reports to ensure the scientific and rigorous nature of the study results. The implementation process includes: 1. patient screening and enrollment: screen patients who meet the criteria, obtain informed consent, and randomize the group; 2. pain assessment: use VAS to assess pain and record scores; 3. epidural placement: anesthesiologists perform placement and ensure safety; 4. implementation of analgesic program: the control group uses continuous

epidural infusion, and the experimental group performs intermittent epidural injection of local anesthetics on demand; 5. pain management and monitoring: monitor the pain response, and provide data analysis using professional statistical software to ensure that the results of the study are scientific and provide a report. Pain management and monitoring: monitoring pain reactions, handling feedback, adjusting the treatment plan, and recording adverse reactions. Nurse-led epidural analgesia program: the research team and implementation process is shown in [Figure 3](#).the consort diagram of the trial is shown in [Figure 4](#).

[figure not shown]

Figure 2: Nurse-Led Epidural Analgesia Protocol: Research Team and Implementation Process

[figure not shown]

Figure3: The patient study participation pathway

## 10. Study environment and population

This study was conducted in the Pancreatitis Diagnostic and Treatment Center of Guizhou Province, China, which is a multidisciplinary center in collaboration with Anesthesia, Nursing, Traditional Chinese Medicine, Imaging, Ultrasound, Intervention, Nutrition, Clinical Pharmacy, etc. With two comprehensive ICUs and a total number of beds up to 70, this center is dedicated to comprehensively cover the whole process of pancreatitis patients from the

consultation, examination, diagnosis, treatment, rehabilitation, and follow up, and to provide the patients with convenient whole process of precise diagnostic and treatment services. The population of this study consisted of awake SAP patients.

#### **11. Recruitment, screening, and enrollment**

The research team will recruit SAP patients who meet the initial inclusion criteria in the ICU, and the recruitment information will be announced through the Internet, and the study will be introduced to the patients or their legal representatives with the consent of the patients' families to obtain the intention to participate. For interested patients, members of the study team will conduct a detailed assessment based on the inclusion and exclusion criteria, including age, diagnosis, medical history, and laboratory findings, to determine whether they meet the inclusion criteria and record the reasons for exclusion. Patients who meet the inclusion criteria will be introduced in detail by members of the research team with information on the purpose, methods, potential risks and benefits of the study, and after ensuring that they fully understand and sign the informed consent form, they will be formally enrolled in the study and entered into the control or experimental group according to the random allocation scheme. Throughout the process, the research team will strictly follow the ethical principles, protect patients' rights and interests, and record the operation process and results of each step in detail for subsequent data analysis and quality control.

##### **Inclusion criteria**

- (1) Patients aged  $\geq 18$  years and  $\leq 65$  years.
- (2) Patients with a clear diagnosis of SAP.
- (3) Pain score (VAS-P) greater than 3.
- (4) Informed consent signed by the patient or his/her legal representative.

##### **Exclusion criteria**

- (1) Spinal deformity, inappropriate for epidural puncture, failure of thoracic epidural puncture.
- (2) Patients with chronic SAP, patients with SAP combined with pregnancy, patients with pancreatic pseudocyst and infection.
- (3) Patients with contraindications to epidural analgesia, such as coagulation disorders, local infection, allergy to lidocaine, etc.
- (4) Combined with severe cardiac, pulmonary, hepatic and renal failure, serious infection, malignant diseases and autoimmune diseases.
- (5) Patients with incomplete medical records.

Dropout criteria

- (1) The duration of epidural placement is less than 3 days.
- (2) The patient withdraws informed consent for any reason during the study.
- (3) Unable to continue to complete the study for other reasons, such as a change in condition requiring transfer to or discharge from the hospital or refusal of further treatment or evaluation.

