## 12. Sample size

This study is a randomized controlled trial, and the primary outcome indicator is the VAS-P score. From the literature review, it is known that the mean VAS-P scores after the intervention of similar control group protocols are 1-3, and there is no study similar to the experimental group, and the mean VAS-P scores of the pre-experimental group are 1-2. It is proposed to formulate the standard deviation of the two groups combined  $\sigma = 2.5$ , and it is expected that the pain symptom scores of the experimental group can be decreased by  $\delta = 2$ . Setting a bilaterality of  $\alpha = 0.05$ , the degree of certainty is 90%, and based on the formula of the sample size [Formula 1](#), the sample size is calculated for each group of  $N = 33$  participants. Assuming a 15% dropout rate, a total of 76 participants were needed based on a 1:1 randomization ratio.

*Formula 1:*

$$n = \frac{2(z_{\alpha} + z_{\beta})^2 + \sigma^2}{\delta^2}$$

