## 13. Randomization

The study participants were evenly divided into the control group and experimental group using random numbers generated with SPSS 29.0 software. Randomization will be performed by an unblinded study coordinator who does not perform any intervention or outcome assessments. Research staff, with no clinical involvement in the trial, will be responsible for keeping the random allocation list and preparing sealed, opaque sequentially numbered envelopes, each containing a random number denoting the allocated treatment. Participants meeting the inclusion criteria will randomly select a sealed envelope containing the intervention protocol.

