## **19.Primary outcome measure**

Visual Assessment Scale-Pain (VAS-P): which consists of a 100-mm straight line, with one end indicating “no pain at all” and the other end indicating “the most severe pain imaginable”, with the patient marking the corresponding position on the line to represent his/her pain level. Patients marked the corresponding position on the line to represent their pain level. The data were collected by the data collectors at the specified time points (0h, 1h, 6h, 12h, 24h, 48h, 72h). Among them, 0h was before epidural placement, and the other times were 1h, 6h, 12h, 24h, 48h and 72h after epidural placement.

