## **21.Adverse Events**

Puncture-related AE : Healthcare workers observe and record the following 8 indicators during daily care and examination: spinal cord and nerve root injury, epidural hematoma, puncture site infection, total spinal anesthesia, headache after dural puncture, intradural infection, catheter blockage, catheter breakage and ectasia. The number of cases of AE was counted for the period of epidural placement.

Drug-related AE: Pain management nurses observed and recorded the following 8 indicators after the patient's medication: anaphylaxis, hypotension, nausea/vomiting, itching, tremor, sensory disturbances in the lower limbs, fever, decreased oxygen saturation, bradycardia or tachycardia. The statistical methods and times were the same as those for puncture-related AE.

22.Outcome Indicators

Puncture surgery rate (PSR): Calculate the ratio of the number of successful puncture cases to the total number of punctures, which was counted by the data collector.

Length of stay in ICU (ICU-LOS): when patients are transferred out of ICU, the total number of days of ICU stay is recorded.

28-day mortality rate (28D-MR): count the number of patients who died within 28 days and calculate the 28-day mortality rate.

Satisfaction with analgesic effect (SAE): patients' satisfaction with the analgesic effect was assessed using a 0-10 scale, with 0 indicating very dissatisfied and 10 indicating very satisfied. It was collected by the data collector on the day of epidural tube removal.The intervention and data collection process are shown in [Figure 4](#).

[figure not shown]

Figure 5: Intervention and Data Collection Process

23. Quality control

(1) All staff must undergo standardized training and pass assessments to ensure consistent implementation of the intervention, minimizing both executor and assessor bias.

(2) Collected data will be cross-verified by two researchers before being entered into the system to ensure data accuracy.

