In this study, faced with the problem of missing data, we would first try to obtain the missing data through retrospective collection. If this approach fails to work, we will take appropriate measures to deal with the problem depending on the nature of the missing data. For random missing data from consecutive repeated measurements, we can estimate this by calculating the average of the time points before and after the missing

data. If data are missing on two consecutive occasions, the patient's data are considered incomplete and the patient will be excluded. For data that are not missing at random, we will choose an appropriate interpolation method, such as the maximum deviation method or the Verbeke and Molenberghs method, on a case-by-case basis. When choosing interpolation methods, we will consider the distributional characteristics of the data and the missing mechanism to ensure the reliability and validity of the interpolation results.

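### Randomised patients can be dropped for events that follow randomisation (catheter in place under 3 days, transfer or discharge, two missed measurements in a row), which can bias VAS-P and conflicts with several outcomes

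*Protocol*

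**What the plan says.** **Order of events.** Section 9 of the Protocol puts screening, consent and allocation in step 1 ("obtain informed consent, and randomize the group"), pain assessment in step 2 and epidural placement in step 3. Section 11 also allocates directly after consent. Section 19 measures VAS-P at 0, 1, 6, 12, 24, 48 and 72 h, with 0 h before placement.

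**Removal rules.**
- Exclusion criterion (1) in section 11 reads "Spinal deformity, inappropriate for epidural puncture, failure of thoracic epidural puncture". The last item can be known only after the puncture.
- Dropout criterion (1) in section 11 is "The duration of epidural placement is less than 3 days". Criterion (2) is withdrawal of consent. Criterion (3) covers inability to complete the study, for example a change in condition that leads to transfer or discharge.
- Under section 24, a single missing reading is replaced by the average of its neighbours. After two consecutive missing readings the patient's "data are considered incomplete and the patient will be excluded".

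**Outcomes that these rules touch.** The puncture success rate (PSR, section 22) is defined as follows: "Calculate the ratio of the number of successful puncture cases to the total number of punctures". Days of epidural placement (NDEP, section 20) run from insertion to removal. Adverse events (section 21) are counted while the catheter is in place. The 28-day mortality rate (28D-MR, section 22) counts deaths within 28 days.

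**Sample size.** Section 12 gives 33 per group, and 76 in total after a 15% dropout allowance.

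**The concern.** How long a catheter stays in, whether a patient is transferred, and whether two readings in a row are missed are all settled after allocation and during treatment. The arms differ in how extra drug is given (section 17), so these events may occur at different rates in the two arms. They may also be related to pain or to complications. Section 21 lists catheter blockage and breakage, infection, haematoma and hypotension as adverse events. It is plausible that some of these end placement early, although the protocol does not say so. Early recovery could do the same and would push any bias the other way.

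If such patients are removed, the groups compared are no longer the groups randomised. All three hypotheses in section 7 rest on that comparison: VAS-P and intra-abdominal pressure; adverse events, ICU stay and mortality; and satisfaction. Section I cites mortality as high as 30% in the more severe forms of the disease, so early deaths cannot be assumed to be negligible.

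**Working it through.** **1. Which patients the stated rule removes.** The last two VAS-P times are 48 h and 72 h. A patient who dies or leaves observation before 48 h misses both, which is two consecutive occasions, and section 24 excludes that patient. This does not depend on how the dropout list in section 11 is read.

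**2. Rules set against outcomes.**

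| Outcome | What it needs | Rule in conflict |
|---|---|---|
| PSR | failed punctures in the denominator | exclusion (1) removes failed punctures |
| NDEP | all durations, short ones included | dropout (1) applies below 3 days |
| 28D-MR | all deaths within 28 days | section 24 excludes deaths before 48 h |

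**3. The planned sample size.** Inputs from section 12: δ = 2, σ = 2.5, two-sided α = 0.05, power 90%.

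n = 2(1.960 + 1.282)² × 2.5² / 2² = 32.84, so 33 per group. Then 33 × 1.15 = 37.95, so 38 per group and 76 in total. Both stated figures reproduce.

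**4. Power with and without removal** (normal approximation).
- All 76 analysed: 2 / (2.5 × √(2/38)) = 3.487, and Φ(3.487 − 1.960) = 93.7%.
- 15% removed: 76 × 0.85 = 64.6, or 32.3 per arm. 2 / (2.5 × √(2/32.3)) = 3.215, and Φ(3.215 − 1.960) = 89.5%.

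On the protocol's own inputs, keeping everyone costs no power.

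**5. Possible size of the bias.** The documents give no removal rate by arm, so these are assumptions: SD 2.5, 38 per arm, no true difference, a simple t-test, and higher-pain patients more likely to be removed. If a fraction f of an arm is removed and removal has correlation ρ with VAS-P, that arm's mean falls by about ρ × 2.5 × φ(z₁₋f)/(1 − f). For f = 0.15 and ρ = 1 this is 2.5 × 0.233/0.85 = 0.69; for ρ = 0.5 it is 0.34. For 7 against 4 removed at ρ = 0.5, the two arms fall by 0.41 and 0.25, and the unrounded difference is 0.15. Simulation agrees with these shifts and gives the type I error:

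| Removed (arm 1 vs arm 2) | Share of the 76 | ρ | False difference | Type I error |
|---|---|---|---|---|
| 6 vs 0 | 7.9% | 1 (extreme) | 0.69 | 25% |
| 6 vs 0 | 7.9% | 0.5 | 0.34 | about 9% |
| 7 vs 4 | 14.5% | 0.5 | 0.15 | about 6% |
| equal numbers | – | same in both arms | 0 | no mean bias |

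The planned effect is 2 points.

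**The case against.** **The dropout list does not say that dropouts leave the analysis.** This stands. Section 11 only labels them. A reader might take the 15% allowance as confirmation, but trials that analyse everyone also inflate for missing data, and analysis sets are often left to a statistical analysis plan. Section 24, however, says outright that patients are excluded.

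**Section 24 reserves other methods for data not missing at random,** so its exclusion might be meant only for random gaps. The sentence on two consecutive missing readings carries no such limit. As written, it reaches patients who die early.

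**Deaths and adverse events may be counted anyway.** The definition of 28D-MR has no carve-out for dropouts, the schedule in section 35 ties it to ICU transfer or day 28, adverse events cover the whole placement period however short, and section 25 has serious events recorded. A reader might infer that early deaths certainly vanish from 28D-MR. The documents support only a conflict that must be reconciled.

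**PSR need not be 100%, nor NDEP at least 3 days.** It is tempting to say that both follow by construction. They do only if excluded patients are left out of those counts, and the PSR denominator could be all punctures.

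**Failed puncture should not bias VAS-P much.** This stands. It happens before treatment diverges, since both arms start on the same continuous infusion. Its harm is to PSR.

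**Exclusion (5), incomplete medical records,** reads as a screening criterion and is not part of this point.

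**The 25% figure is an extreme.** This stands. It takes losses in one arm only, fully determined by VAS-P. The planned analysis is repeated-measures ANOVA, so the t-test figures are indicative only.

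**Conclusion.** The point holds for the 3-day and change-in-condition dropout criteria and for the exclusion after two consecutive missing readings. All act after randomisation. Only the last is stated as removal from the data; for the others it is a reading of the text. Such removals can bias the VAS-P comparison and understate adverse events and deaths. Neither size nor direction can be known from the documents. Under the assumptions shown, the false difference ranges from none (equal removal), through 0.15 to 0.34 points with type I error of about 6% to 9% at correlation 0.5, to 0.69 points and 25% in the extreme case. The definitions of PSR, NDEP and 28D-MR must be reconciled with the removal rules whatever the size of the bias. A later analysis plan could not fully repair this: it would have to override section 24, and it could not recover readings that were never taken.

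**What to change.** 1. **Analysis.** Delete the exclusion for two consecutive missing values in section 24. State that dropout criteria (1) and (3) do not remove a patient from analysis. Analyse all randomised patients in the allocated arm with all available VAS-P data, for example by a likelihood-based repeated-measures model. Keep the subset with 3 days or more of placement as a sensitivity analysis.
2. **Follow-up.** Continue VAS-P to 72 h after early catheter removal where possible. Record adverse events, ICU stay and day-28 status for every randomised patient, except where consent to further data collection is withdrawn.
3. **Timing of allocation.** Open the envelope after successful catheter placement. Both arms begin on the same infusion, and the 0 h reading is already taken before placement. Failed puncture then becomes a true pre-randomisation exclusion. Report PSR descriptively over all punctured patients.

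Item 3 can apply only to patients not yet randomised. Items 1 and 2 can be made by amendment if recruitment has begun.

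**Cost.** There is slightly more follow-up of patients whose catheter comes out early, and the estimated effect may be smaller than in the selected subset. No extra patients are needed, and no treatment rule changes.

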## 12. Sample size

This study is a randomized controlled trial, and the primary outcome indicator is the VAS-P score. From the literature review, it is known that the mean VAS-P scores after the intervention of similar control group protocols are 1-3, and there is no study similar to the experimental group, and the mean VAS-P scores of the pre-experimental group are 1-2. It is proposed to formulate the standard deviation of the two groups combined  $\sigma = 2.5$ , and it is expected that the pain symptom scores of the experimental group can be decreased by  $\delta = 2$ . Setting a bilaterality of  $\alpha = 0.05$ , the degree of certainty is 90%, and based on the formula of the sample size [Formula 1](#), the sample size is calculated for each group of  $N = 33$  participants. Assuming a 15% dropout rate, a total of 76 participants were needed based on a 1:1 randomization ratio.

*Formula 1:*

$$n = \frac{2(z_{\alpha} + z_{\beta})^2 + \sigma^2}{\delta^2}$$

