## **27. Limitations:**

This study is a single-center trial, which may limit the generalizability of the study results. Although the sample size calculation ensures statistical power, it may still be insufficient to detect small but clinically significant

differences. Additionally, the study relies on the accurate assessment of pain using the Visual Analog Scale for Pain (VAS-P), which may be subject to patient subjective interpretation. There may also be data missing due to patient withdrawal or other unforeseen circumstances, which could affect the robustness of the results. Furthermore, the study duration may not be long enough to fully capture the long-term effects of the intervention.

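### The 90% power rests on a 2-point difference that the protocol's own expected means reach only at their most favourable ends

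*Protocol*

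**What the plan says.** Protocol Section 12 (Sample size) takes VAS-P as the primary outcome and gives two pieces of prior information. From the literature, "the mean VAS-P scores after the intervention of similar control group protocols are 1-3". For the new regimen, "there is no study similar to the experimental group, and the mean VAS-P scores of the pre-experimental group are 1-2".

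It then fixes the planning values. The SD is introduced with "It is proposed to formulate the standard deviation of the two groups combined" and set at 2.5, without a source. The effect is introduced with "it is expected that the pain symptom scores of the experimental group can be decreased by" and set at δ = 2. With two-sided α = 0.05 and 90% power, Formula 1 is said to give 33 per group, and a 15% dropout allowance brings the total to 76.

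Section 27 (Limitations) begins its remark on size with "Although the sample size calculation ensures statistical power", then concedes that differences which are small but clinically important may be missed.

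**The concern.** Formula 1 is a two-group formula, so δ has to be the difference between the arms. The two ranges of means quoted just before it do not yield 2 except at one corner. The protocol does not derive the 2 from those ranges, does not present it as a minimal clinically important difference, and cites nothing for it.

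The wording also leaves open that the 2 is a fall from baseline within the experimental group. That would not help: the control group is also on epidural analgesia and is also expected to improve, so a within-group fall is not the quantity the two-group formula needs.

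At stake is how the result is read. With 90% power on record, a non-significant result would be taken as fairly strong evidence against any useful benefit. The protocol's own inputs support that reading for a 2-point benefit and not for smaller ones that lie equally within its expected means.

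**Working it through.** **Inputs, all from Section 12.** Control mean 1 to 3; pre-experimental mean 1 to 2 (read as pilot data on the experimental regimen); δ = 2; SD σ = 2.5; two-sided α = 0.05; power 90%; 33 per group; 15% dropout; total 76. All scores are taken to be in the same points.

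**1. Reproduce the stated size.** The standard formula is n = 2(z₀.₉₇₅ + z₀.₉₀)²σ²/δ².
- (1.960 + 1.282)² = 10.51, and twice that is 21.01.
- 21.01 × 6.25 / 4 = 32.8, rounded up to **33 per group**. The stated figure reproduces.
- Formula 1 as printed adds σ² instead of multiplying: (21.01 + 6.25)/4 = 6.8, which is **7 per group**. So 33 came from the standard formula and not from the one shown.

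**2. Differences that the quoted means allow (control minus experimental).**
- Largest: 3 − 1 = **+2**
- Smallest: 1 − 2 = **−1**
- Midpoints: 2.0 − 1.5 = **0.5**

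Seen the other way, taking 2 off the control range gives −1 to 1, which meets the pre-experimental range of 1 to 2 only at the value 1.

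**3. Power at 33 per group.** Two-sample t-test at one time point, 64 degrees of freedom, critical value 1.998, noncentrality δ/(σ√(2/33)). At σ = 2.5 the standard error is 2.5 × √(2/33) = 0.615.

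| True difference | SD 2.5 (stated) | SD 2.0 | SD 1.5 |
|---|---|---|---|
| 2.0 | 89% | 98% | >99% |
| 1.5 | 67% | 85% | 98% |
| 1.0 | 36% | 52% | 76% |
| 0.5 | 13% | 17% | 27% |

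The normal approximation gives 90.1% for 2 points at SD 2.5, which is the protocol's 90%. The SDs of 2.0 and 1.5 are my assumptions, included to show how far the result depends on that input.

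**4. Repeated measures.** Section 24 plans a repeated-measures ANOVA over seven time points. As a rough guide, suppose the same difference at all six post-baseline times and an assumed within-patient correlation ρ. The SD of the six-time mean is then 2.5 × √((1 + 5ρ)/6):
- ρ = 0.3: SD 1.61, power 71% for 1 point and 24% for 0.5
- ρ = 0.7: SD 2.17, power 47% for 1 point and 15% for 0.5

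**5. Dropout.**
- 33 × 1.15 = 37.95, so 38 per group and 76 in total, which matches the protocol.
- Applying a 15% loss to 76 leaves 76 × 0.85 = 64.6, about **32 per group**. Power for 2 points is then 88%.
- Keeping 33 after the loss would take 33/0.85 = 38.8, so 39 per group and 78 in total.

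**The case against.** The strongest reply is that the calculation is internally valid: given δ = 2 and SD 2.5, 33 per group at 90% is correct. That stands. The fault lies in the δ that was fed in, not in the arithmetic.

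Several further points limit how far the criticism can go.

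- **The true power is not known to be low.** A reader might infer that the trial's real power is about 13%. The documents do not support that. The cited means are ranges without time points or weights, and the midpoints are a convenient reference, not the protocol's forecast.
- **The SD may be too large.** It is unsourced and looks generous beside means of 1 to 3 on a scale that cannot go below zero. A smaller SD helps: 1 point has 76% power at SD 1.5. The protocol offers no smaller value, however, and 0.5 points stays at 27%.
- **Repeated measures may add power.** They may, but under the assumed correlations 1 point stays below 90%.
- **A null result would still say something.** A reader might infer that it would be uninformative. At SD 2.5 and 33 per group, the 95% confidence interval has a half-width of about 1.998 × 0.615 = 1.23 points, so an observed difference near zero would exclude 2 points. It would leave benefits of around 1 point open.
- **Section 27 already carries a caveat.** It does, and this partly covers the point. But a 1-point difference, well within the protocol's own expected means, is not obviously among the small differences that Section 27 has in mind.
- **The + in Formula 1 changes no number that was used.** True. If the sponsor's master copy shows multiplication, that item falls away.

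**Conclusion.** The point holds in conditional form. The stated 90% power applies to one corner of the protocol's own expectations: control at the top of its range and experimental at the bottom. At the stated SD, power falls to about 67% for 1.5 points, 36% for 1 and 13% for 0.5. This rests on 33 analysed per group, SD 2.5, a two-sided 5% t-test at one time point, and reading the pre-experimental group as pilot data on the new regimen. A smaller SD or the repeated-measures analysis would raise these figures by amounts the protocol does not allow one to fix.

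Two lesser errors sit in the same section. The printed formula gives 7 instead of 33. The dropout allowance leaves about 32 per group instead of 33, which costs about one percentage point of power (89% to 88%).

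**What to change.** 1. In Section 12, say that δ is the between-group difference, claim about 90% power for 2 points only, and identify that value as the most favourable reading of the cited means. If there is a clinical reason for 2 points, give it.
2. Add power at 0.5, 1 and 1.5 points over a range of SDs, such as the table above, and give the source of the SD of 2.5 or say that it is assumed.
3. Qualify the power statement in Section 27 so that it refers to a 2-point difference and no longer reads as a general assurance.
4. Correct Formula 1 to n = 2(z_α + z_β)²σ²/δ², with z_α stated to be the two-sided value.
5. State that 76 patients with 15% loss leave about 32 per group, with about 88% power for 2 points.

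The cost is a less favourable stated power. The number of patients, the endpoint and the analysis do not change.
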